### 3.3 Description of treatments

#### 3.3.1 Study Medication

Description: Miltefosine is formulated as capsules in two dosages: 10 mg or 50 mg. These are packaged in blister packs containing 7 capsules; the blisters are packed in boxes of 8 units. The investigator or authorized person means a box for an eligible patient by writing the initials of the patient on the box label, ie, the capsules contained in a box are for use only a single patient, residual capsules can not be used by a another patient.

The batch number is documented in the certificate of analysis, to be held in the master file of the study, a copy will be included in *the investigator's file*.

Re-examination or expiration date: The medication must be used after re-examination or expiration date that is specified on the analysis certificate. The monitor of the study should commence appropriate measures in due time if the study medication is needed after that date. Should be made with written notice about the extent of the review / expiry date.

Responsibility at the center of the study: The researcher is responsible for proper storage and distribution of products in research and observe the relevant pharmaceutical regulations. The researcher must nominate a responsible person to care for the study medication.

Storage: The medication should be kept out of reach of children and protected from direct sunlight.

#### 3.3.2 Appointment to the processing and recording

Patients who have been included in evaluations of selection for this research will be documented in an identification list + Patient Record Selection / enrollment.

Each eligible patient will be designated by consecutive numbers, starting at 1 for each age group. The number of patients will be documented in the List of ID + Patient Record Selection / enrollment.

Registration and randomization: the treatment will be allocated according to a randomization list generated by the biostatistics program.

Home Treatment: Treatment should be started up within 2 weeks after completion of evaluations of selection. Otherwise meeting the criteria for eligibility will be restored.

#### 3.3.3 Administration of study treatment

##### Miltefosine

The dose and dosing schedule will be as follows:

Via: Oral

Dose for Target dose of 2.5 mg / kg body weight per day;  
Group 1: daily dose rounded to the next increment of 10 mg;  
Patients over 20 kg will receive 1 capsule of 50 mg per day

Dose for Patients > 25 kg body weight: 100 mg / day, or one capsule of 50 mg in the morning and one  
Group 2: capsule of 50 mg at night and after meals

Patients <25 weight: 50 mg / day, ie a capsule of 50 mg in the morning after meal

Duration: The duration of study treatment is 28 days

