#### 3.2.1 Inclusion criteria

- Newly diagnosed (untreated) cutaneous leishmaniasis with localized lesions and visualization of amastigotes in tissue samples or a positive culture or diagnosed by polymerase chain reaction (PCR) methods or by intradermal skin testing (Montenegro test)
- Number of lesions: 1 to 5 ulcerative lesions
- Lesion's diameter: 1 to 5 cm.
- Age: **Group 1: 2 to 12 years; Group 2: 13 to 65 years**
- Sex: male and female patients eligible (no effort to be made to balance the study for gender)

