#### Modifications in the treatment

Reduce dose: A patient who does not tolerate the dose of Miltefosine used, will leave the treatment. No dose reduction is planned.

Discontinuation of study treatment: The criteria for withdrawal are presented in section 4.2.3.

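### The Group 1 miltefosine rule contradicts itself above 20 kg (flat 50 mg against a 2.5 mg/kg target), and above 25 kg it gives half the Group 2 dose at equal weight

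*Protocol*

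**What the plan says.** The age groups are defined in Protocol section 3.2.1 as "Group 1: 2 to 12 years; Group 2: 13 to 65 years". Section 3.3.3 (Miltefosine) then doses them by different rules.

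- **Group 1:** "Target dose of 2.5 mg / kg body weight per day", with the "daily dose rounded to the next increment of 10 mg", followed by "Patients over 20 kg will receive 1 capsule of 50 mg per day". No upper weight is attached to the last line, and it is not called a maximum.
- **Group 2:** "Patients > 25 kg body weight: 100 mg / day" and "Patients <25 weight: 50 mg / day". No mg/kg target is stated for this group.

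In the text available the group labels are interleaved with the dose lines, but the assignment is still readable: the 10 mg rounding line follows the Group 1 label, and the rest of the morning-and-night regimen follows the Group 2 label.

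Two other places bear on the point. Section 3.3.1 says "Miltefosine is formulated as capsules in two dosages: 10 mg or 50 mg". Under Modifications in the treatment the protocol says "No dose reduction is planned". Neither reconciles the Group 1 target with the rule for patients over 20 kg.

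**The concern.** The Group 1 text gives a target in mg/kg and, for the heavier children, a fixed dose that cannot meet it. A site that follows the target and a site that follows the flat rule would give different doses to the same child.

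The split between the two rule sets is by age alone. Above 25 kg, being on one side or the other of the 13th birthday changes the daily dose by a factor of two at unchanged weight.

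The statistical stake is that age and exposure become entangled within the miltefosine arm. Section 2 states the primary endpoint, final cure at 6 months, without an age split. If cure or adverse events differ between children and older patients on miltefosine, part of the difference may reflect the dosing rule rather than age. The protocol would offer no stated reason for that difference in exposure.

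**Working it through.** **Inputs** (Protocol sections 3.2, 3.2.1, 3.3.1 and 3.3.3): Group 1 target 2.5 mg/kg/day with 10 mg rounding; Group 1 flat dose 50 mg/day over 20 kg; Group 2 dose 100 mg/day above 25 kg and 50 mg/day below 25 kg; capsules of 10 mg and 50 mg; 30 of 90 patients planned for Group 1; overall allocation 2:1.

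**Step 1: where 50 mg meets the target.** Target dose = 2.5 × weight. At 20 kg this is 2.5 × 20 = 50 mg, so the flat dose is reproduced at exactly that weight.

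**Step 2: can rounding explain 50 mg above 20 kg?** Rounding up cannot: at 20.5 kg the target is 51.25 mg, which rounds up to 60 mg. Rounding to the nearest 10 mg gives 50 mg only up to 22 kg, where the target reaches 55 mg.

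**Step 3: dose delivered.** Delivered mg/kg = daily dose / weight; percentage of target = delivered / 2.5.

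| Weight (kg) | Group 1 target (mg) | Group 1 at 50 mg (mg/kg) | % of Group 1 target | Group 2 dose (mg) | Group 2 (mg/kg) |
|---|---|---|---|---|---|
| 20 | 50 | 2.50 | 100 | 50 | 2.50 |
| 22 | 55 | 2.27 | 91 | 50 | 2.27 |
| 24 | 60 | 2.08 | 83 | 50 | 2.08 |
| 25 | 62.5 | 2.00 | 80 | none stated | – |
| 30 | 75 | 1.67 | 67 | 100 | 3.33 |
| 35 | 87.5 | 1.43 | 57 | 100 | 2.86 |
| 40 | 100 | 1.25 | 50 | 100 | 2.50 |

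The weights are illustrative, because the protocol gives none by age. At 20 kg itself the Group 1 dose comes from the target rule, since the flat rule applies only over 20 kg.

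**Step 4: the step between age groups.** At any weight above 25 kg the ratio is 50/100 = 0.5. Over 20 and under 25 kg it is 50/50 = 1, so there is no step. At exactly 25 kg neither Group 2 line applies, because one is written with > and the other with <.

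**Step 5: how many patients.** Group 1 controls receive antimony and are unaffected. If 2:1 holds within Group 1 (section 3.2 states it only overall), 30 × 2/3 = 20 children receive miltefosine. Of these, only those over 20 kg are affected, so 20 is an upper figure under that assumption.

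**The case against.** The strongest reply is that the Group 1 text can be carried out as written: a general target with a specific override for heavier children. The 20 kg threshold is exactly where the target reaches 50 mg, which is what an unlabelled cap would look like. This is a fair reading, and it means a site could dose every child. It does not remove the conflict. The text does not call 50 mg a maximum, whereas the antimony section does label its own maximum daily dose. A cap would still leave heavier children below the group's stated target and would not explain the doubling at age 13. Capsule sizes do not force it either, since 10 mg capsules are supplied.

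A second reply is that falling mg/kg is a property of any flat dose. Group 2's 100 mg gives 100/60 = 1.67 mg/kg at 60 kg and 100/80 = 1.25 at 80 kg, the same as a Group 1 child at 30 and 40 kg. That stands: varying exposure is not peculiar to Group 1. What is peculiar to Group 1 is a stated target that its own flat rule misses.

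A third reply is that exposure can be recovered, because body weight is recorded (sections 3.4 and 4.1). That also stands, although a group of about 20 limits what can be learned from it.

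The gap at exactly 25 kg may be no more than a slip in the inequality signs. It is minor by itself.

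**Conclusion.** The concern holds in a limited form. In Group 1 the stated target and the stated dose over 20 kg disagree at every weight where the flat rule applies, apart from what nearest-10 mg rounding would absorb below 22 kg. The shortfall grows with weight: 20% at 25 kg, 33% at 30 kg and 50% at 40 kg. The two-fold step between age groups at equal weight is exact, but exists only above 25 kg. These results are arithmetic on the protocol's own figures and need no outside data.

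A reader might infer more, and the documents do not support it:

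- **That Group 1 as a whole receives about half its target.** No weights are given. Half applies at 40 kg, and children a little over 20 kg fall only slightly short.
- **That all 30 Group 1 patients are affected.** Only miltefosine-arm children over 20 kg are, at most about 20 if 2:1 holds within the group.
- **That every 12-year-old gets half the dose of a 13-year-old of the same weight.** Over 20 and under 25 kg the doses are equal.
- **That a low cure rate in children could never be separated from low exposure, or that a pooled comparison is thereby invalid.** Weight is recorded, and the protocol does not specify how the age groups are combined.

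Nor do the documents show which line is the intended one. The finding is that they conflict.

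**What to change.** Before enrolment, the sponsor must reconcile three items in section 3.3.3 and state which governs: the Group 1 mg/kg target with its rounding, the Group 1 rule over 20 kg, and the Group 2 weight rule, including a patient of exactly 25 kg. If the difference between age groups at equal weight is intended, the protocol should say so and give the reason. No dose or rule is proposed here.

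As an optional addition, report final cure by age group alongside the mg/kg/day received, calculated from the body weight already recorded, and note that the small group makes this descriptive only.

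The cost is a wording amendment and one descriptive table. No new data, visits or patients are needed.

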##### Standard treatment - Pentavalent Antimony (Glucantime ®)

Pentavalent antimony: with 5ml ampoules containing 81mg of pentavalent antimony (Sbv) per ml:

Dose 20mg/Sbv / kg / day administered intramuscularly or by intravenous injection (no need for dilution, application must be slow: last for about 5 minutes). It is necessary to rest after application.

Note: maximum daily dose for adults is 3 ampoules or 1.275mg Sbv.

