### 3.2 Study population

It is planned to include in this study 90 patients, with 30 patients in Group 1 (2 to 12 years old) and 60 patients in Group 2 (13 to 65 years old). Of this total, 60 patients will receive the study drug (Miltefosine), while the remaining 30 will be part of the control group (receive Glucantime®). Ratio miltefosine / standard : 2/1.

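### The antimony strength and the adult milligram cap for the control arm cannot both be right: three ampoules hold 1,215 mg at 81 mg/ml, not 1,275 mg

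*Protocol*

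**What the plan says.** The control dosing is set out in one place, the standard treatment part of protocol section 3.3.3. The drug comes "with 5ml ampoules containing 81mg of pentavalent antimony" per ml. The dose is 20 mg of antimony per kg per day, given by the intramuscular or intravenous route without dilution. A note then limits the dose: the "maximum daily dose for adults is 3 ampoules or 1.275mg" of antimony. The wording presents the ampoule count and the milligram figure as two expressions of one limit.

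Section 3.2 puts 60 patients on miltefosine, "while the remaining 30 will be part of the control group". It plans 30 of the 90 patients in the 2 to 12 year age group. No other section gives a strength or a maximum dose for the control drug.

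**The concern.** Ampoule volume, strength, ampoule cap and milligram cap are tied together by simple multiplication, and the stated values do not multiply out. A prescriber who works from the milligram cap and one who works from the ampoule cap reach different maximum doses. A prescriber who converts 20 mg/kg into millilitres relies on a strength that the cap contradicts.

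These are operative instructions for the active control, the comparator for the primary endpoint. Section 5.2 itself describes antimonial toxicity as sometimes severe and names pancreatitis and cardiac arrhythmias, so the dosing line should allow only one reading. Drug strength and maximum dose belong in the protocol and would not be settled by a statistical analysis plan.

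**Working it through.** **Inputs, all from section 3.3.3:** 5 ml per ampoule; 81 mg/ml; 20 mg/kg/day; adult cap of 3 ampoules, equated with 1.275 mg as printed.

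**Reproducing the stated cap.** Ampoules × ml per ampoule × mg per ml = 3 × 5 × 81 = 1,215 mg.
- Taken literally, 1.275 mg is too small by a factor of about 950 (1,215 / 1.275).
- With the point read as a thousands separator, or the unit as grams, the cap is 1,275 mg. The gap is 1,275 − 1,215 = 60 mg, and 60 / 1,215 = 4.9%.

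Neither reading reproduces the figure. The rest of the check uses the favourable one, 1,275 mg.

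**Solving backwards.** The strength at which three ampoules hold 1,275 mg is 1,275 / (3 × 5) = 85 mg/ml exactly. At 81 mg/ml, 1,275 mg would need 1,275 / 81 = 15.74 ml, or 15.74 / 5 = 3.15 ampoules.

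**Case A: 81 mg/ml is right and the milligram cap is wrong.** The ampoule cap starts to bind at 1,215 / 20 = 60.75 kg and the milligram cap at 1,275 / 20 = 63.75 kg. Up to 60.75 kg the two caps give the same dose. Above that they diverge, by the full 60 mg from 63.75 kg.

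**Case B: 85 mg/ml is right and the stated strength is wrong.** The volume computed from the protocol is 20 / 81 = 0.247 ml/kg instead of 20 / 85 = 0.235 ml/kg. The dose delivered is (20 / 81) × 85 = 20.99 mg/kg/day, and 85 / 81 − 1 = 4.9% too much. With the 15 ml limit applied:

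| Weight | Target dose | Volume at stated 81 mg/ml | Correct volume at 85 mg/ml | Dose delivered | Excess |
|---|---|---|---|---|---|
| 20 kg (child) | 400 mg | 4.94 ml | 4.71 ml | 419.8 mg | 19.8 mg |
| 60 kg | 1,200 mg | 14.81 ml | 14.12 ml | 1,259.3 mg | 59.3 mg |
| 62 kg | 1,240 mg | 15 ml (limit) | 14.59 ml | 1,275 mg | 35 mg |
| 63.75 kg | 1,275 mg | 15 ml (limit) | 15 ml | 1,275 mg | 0 mg |

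The excess peaks at 60 mg at 60.75 kg, falls to zero at 63.75 kg and stays there, because the 15 ml limit then gives the intended 1,275 mg.

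**Who is affected.** At most the 30 control patients. The protocol gives no body weights, so the number in either case cannot be estimated. If the 2:1 ratio holds within the younger age group (an assumption), 30 / 3 = 10 controls would be children, to whom only case B applies.

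**The case against.** The best counter-argument is that the working limit is clear. Three ampoules can be counted, the ampoule figure comes first, and the milligram figure reads as a gloss. In case A, reaching 1,275 mg would mean opening a fourth ampoule, against the first half of the same sentence. That largely stands for heavier adults. It does not help below about 61 kg or for children, where the adult cap does not act and the stated strength is what turns mg/kg into millilitres.

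Case B does rest on two things that the protocol does not show: a true strength of 85 mg/ml, and staff who calculate from the protocol and not from the ampoule label. Its figures are conditional illustrations, not evidence that anyone was misdosed.

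The printed 1.275 is most naturally a thousands separator in a text translated from Portuguese. That is accepted, and the 60 mg gap remains after it. Rounding does not explain the gap either. A single wrong digit could account for it (81 for 85), but nothing in the document indicates which figure is the slip.

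Finally, the discrepancy does not touch the endpoint, sample size, randomisation or analysis. That is true, and it is why the point is minor.

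**Conclusion.** The concern holds as a minor error. On the protocol's own numbers the control drug's strength and its milligram cap are incompatible, by 60 mg or 4.9%, once the cap is read as 1,275 mg; read literally, the mismatch is far larger. The document does not show which figure is wrong, so the consequence depends on the case: a milligram cap that is too high for control adults above 60.75 kg, or a stated strength that leads to about 5% too much volume for controls below the cap. The explicit three-ampoule limit contains the effect in adults. No effect on cure rates, adverse event rates, power or type I error is claimed.

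**What to change.** Check the label of the product supplied, then restate the line with one consistent set of figures and an unambiguous unit. The two options are:

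- 81 mg/ml, maximum 3 ampoules (15 ml) = 1,215 mg of pentavalent antimony per day; or
- 85 mg/ml, maximum 3 ampoules (15 ml) = 1,275 mg of pentavalent antimony per day.

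The cost is one label check and one corrected line in section 3.3.3. Nothing in the design or analysis has to change.

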#### Modifications in the treatment

Reduce dose: A patient who does not tolerate the dose of Miltefosine used, will leave the treatment. No dose reduction is planned.

Discontinuation of study treatment: The criteria for withdrawal are presented in section 4.2.3.

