### 3.2.3 Criteria for withdrawal

A premature withdrawal or discontinuance shall be construed as withdrawal procedures of the study after the first exposure to study treatment. Withdrawals before that time should be considered "failures of selection."

Patients may be withdrawn from the study at any time at its own request or on the basis of clinical trial investigator. However, patients who request the withdrawal will be strongly encouraged to conduct appropriate tests to make a valid assessment and possible inclusion in the analysis.

The reasons for withdrawal are classified as follows:

**Lack of effectiveness:** The patient showed inadequate response to treatment or deterioration.

**Lack of tolerance:** the dose-limiting intolerance reported by patients or observed by the doctor and found to be "probably" related to study treatment (and therefore does not refer to an aggravation of a preexisting condition).

An adverse event is considered dose limiting toxicity if he understands grade 3 or 4 of the common terminology criteria for adverse events (CTCAE) and is confirmed by a re-assessment within a week.

In the case of treatment of grade 3 transaminase elevation CTCAE, the investigator may decide to continue treatment until no manifestation of liver injury is observed (eg. Jaundice), additional control tests are designed to ensure patient safety.

The CTCAE grade 4 elevation of enzyme (s) impairment (s) or clinical signs of liver damage require immediate discontinuation of study treatment.

**Intercurrent disease:** A disease or condition that occurred or worsened during the study and prevented the completion of treatment and procedures of the study, however, no evidence of a causal relationship to study treatment, the adverse event record corresponding to classify causality as "unlikely" or "not assessable".

**Withdrawal of consent / non-adherence:** The patient, parent or legal guardian withdrew consent or the patient did not adhere to study procedures (must be verified if an adverse event caused withdrawal).

**Other (s) reason (s):** Reason for discontinuation not approached by any of the criteria above, p. ex., moving the patient, other reasons must be specified.

Patients who are withdrawn from the study will not be replaced.

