### **4.3 Assessments at the end of treatment**

The end of treatment will be the 28th day in the case of regular treatment. In case of premature discontinuation, all assessments listed below will be executed whenever the treatment is discontinued.

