| - CBC                                                    |       | x               |       | x     | x      | x      | x                       |                                  | x                                |                                   |                                   |                                   |
| - Biochemistry                                           |       | x               |       | x     | x      | x      | x                       |                                  | x                                |                                   |                                   |                                   |
| - Urine type 1                                           |       | x               |       |       |        |        | x                       |                                  | x                                |                                   |                                   |                                   |
| - ECG (control patients)                                 |       | x               |       |       |        |        | x                       |                                  |                                  |                                   |                                   |                                   |
| Vital signs                                              |       | x               | x     | x     | x      | x      | x                       |                                  | x                                | x                                 | x                                 | x                                 |

a Within the 14 days before the 1st dose (except for parasitological examination of lesions, which will be valid within the last 4 weeks)

b It should be evaluated fully when treatment is discontinued. The reason (s) for discontinuation is (are) documented (s). This applies also to patients who withdrew from the study due to any reason.

c Evaluation of selection performed in the first half of the menstrual cycle (<10 days of the cycle) in the case of a negative pregnancy test before randomization, the treatment can be initiated without waiting period.

Evaluation of selection performed in the second half of the menstrual cycle (> 10 days) pregnancy test followed by a waiting period of two weeks, during which they should be used adequate contraception. After the waiting period should be performed a confirmatory test of pregnancy, before randomization.  

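### Stopping treatment is not clearly separated from leaving the study, and nothing requires the 2- and 6-month assessments after an early stop

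*Protocol*

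**What the plan says.** - **Rule for stopping.** Under Modifications in the treatment (Protocol 3.3.3) the only text is "Discontinuation of study treatment: The criteria for withdrawal are presented in section 4.2.3". Section 4.2 has no numbered subsections; the withdrawal criteria are in 3.2.3.
- **Definition.** Section 3.2.3 opens with "A premature withdrawal or discontinuance shall be construed as withdrawal procedures of the study after the first exposure to study treatment".
- **Reasons.** Section 3.2.3 then classifies them: intolerance ("the dose-limiting intolerance reported by patients or observed by the doctor"), intercurrent disease, poor response ("The patient showed inadequate response to treatment or deterioration"), and a class that joins withdrawal of consent with non-adherence ("the patient did not adhere to study procedures"). Patients who ask to leave are urged to have tests so that they might still be analysed, but no visit is named. Withdrawn patients are not replaced.
- **Assessment at an early stop.** Section 4.3 says "In case of premature discontinuation, all assessments listed below will be executed whenever the treatment is discontinued". Footnote b of the flowchart (4.6) asks for a full evaluation at visit 6 when treatment is discontinued and adds "This applies also to patients who withdrew from the study due to any reason".
- **Content of that assessment.** The 4.3 list holds safety items, the reason for stopping and overall tolerability. The flowchart also marks parasitology, lesion size and photograph at visit 6.
- **Endpoints.** Section 2 sets final cure at 6 months after treatment as primary and initial cure at 2 months as secondary. These are flowchart visits 11 and 9.
- **Later follow-up.** Section 3.4 states monitoring to 6 months for patients with apparent or partial cure. It does not mention patients who stopped treatment early.

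**The concern.** Stopping a drug and ending observation are different events, and a cure rate at a fixed later time depends on keeping them apart. Here one set of criteria serves both. A patient who stops capsules because of vomiting, one who misses injections and one who refuses all further contact can be handled alike, and a site can close the record after visit 6.

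Such exits are unlikely to be unrelated to outcome or arm. Treatment is open-label, inadequate response has no definition in 3.2.3, one drug is oral and the other injected, and their toxicities differ. At stake is the lesion status at 2 and 6 months for just those patients whose course went badly or was incomplete. How to analyse missing outcomes can be left to a statistical analysis plan. Whether the visit takes place is for the protocol to fix.

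**Working it through.** The protocol states no withdrawal rate and no figure on this point, so there is nothing to reproduce. The check has two parts.

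**A. What the text requires after an early stop**

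1. Text that joins the two events: the opening of 3.2.3 and the pointer in 3.3.3.
2. Text that keeps them apart: 3.3.3 has a patient who cannot tolerate miltefosine leave the treatment, not the study. Footnote b names patients whose treatment stopped and then, separately, those who withdrew. Flowchart visit 6 is day 28 or the end of therapy, and visits 7 to 11 are timed from the end of therapy, so they can be dated for an early stopper.
3. Text that requires an assessment after an early stop: 4.3 and footnote b, both for visit 6 only.
4. Text that requires visit 9 (2 months) or visit 11 (6 months) after an early stop: none.

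Follow-up after stopping is thus possible under item 2 but nowhere required, and a site may read item 1 as ending it.

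**B. How much missing status could matter**

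Inputs: 60 miltefosine and 30 control patients (3.2). Assumption: a share *d* of each arm has no 6-month status.

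- Weight of one patient: 1/60 = 1.7 points on miltefosine, 1/30 = 3.3 points on control.
- With *a* observed cures and *m* patients of unknown status among *n*, the arm's cure rate lies between *a*/*n* and (*a* + *m*)/*n*, a width of *m*/*n*.
- The difference between arms is lowest when all unknowns are failures on miltefosine and cures on control, and highest in the reverse case. The two bounds lie *m*₁/60 + *m*₀/30 apart, whatever the cure rates.

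| Assumed share without status | Miltefosine | Control | Distance between bounds |
|---|---|---|---|
| 5% (1.5 controls, taken as 2) | 3/60 = 5.0 | 2/30 = 6.7 | 11.7 points |
| 10% | 6/60 = 10.0 | 3/30 = 10.0 | 20.0 points |
| 20% | 12/60 = 20.0 | 6/30 = 20.0 | 40.0 points |

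These are worst-case limits on what would be unknown. They do not estimate bias.

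**The case against.** The strongest reply is that the protocol already separates the two events. Intolerant patients leave treatment only, footnote b distinguishes stopping from withdrawing, the later visits run from the end of therapy, and the list in 3.2.3 classifies reasons without ordering anyone out, since patients may, not must, be withdrawn. The opening sentence of 3.2.3 is also a rough translation. This reply stands to the extent that exit is permitted, not mandated; a reader who infers that the protocol removes these patients goes too far. It does not close the gap, because none of these places requires visits 9 and 11 after an early stop.

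Three further inferences are tempting, and the document does not support them.

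- *A patient withdrawn for poor response can never meet the definition of clinical failure.* The 3.2.3 category includes deterioration, which may be a new lesion or growth above 50%, both failure criteria in 3.4. The flowchart also has parasitology at visit 6. How 3.4 applies to an exit during treatment is unclear, but that does not mean no criterion can be met.
- *The reported cure rate will be inflated because withdrawals leave the denominator.* The protocol fixes no such analysis set, and the statistical analysis plan is not shown. If exits were equally frequent and of the same kind in both arms, the between-arm comparison need not be biased.
- *Any stop for lack of effectiveness should count automatically as failure.* That would carry an unblinded judgement straight into the primary endpoint. It is also unnecessary for patients whose lesions are still observed.

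The visit 6 mismatch is partly editorial. The 4.2 list likewise omits lesion items that the flowchart marks, and footnote b already asks for a full evaluation.

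**Conclusion.** The point holds as a gap in required data collection. The protocol merges stopping treatment with leaving the study in one place, separates them in others, and nowhere requires the 2- and 6-month lesion assessments after an early stop. Loss of the primary and secondary endpoints for outcome-related reasons is therefore allowed, though not prescribed.

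The actual size is unknown. It depends on how many patients stop early, in which arm, and whether sites follow them anyway. The firm figure is the weight of a single control patient, 3.3 points. The 20-point distance between bounds rests on the assumption that 10% of each arm has no 6-month status and on the most extreme split of the unknowns. The wrong section number is minor by itself, but it sits in the sentence that should settle the matter. The change should be made because it protects both efficacy endpoints at little cost.

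**What to change.** 1. In 3.2.3 and 3.3.3, define stopping study treatment and leaving the study as separate events. State that every treated patient keeps visits 7 to 11, including the lesion assessments at 2 and 6 months, unless consent to follow-up is withdrawn. Separate non-adherence from withdrawal of consent. Early stoppers are then classified from observed lesions by the existing criteria in 3.4.
2. Correct the reference in 3.3.3 from 4.2.3 to 3.2.3.
3. Add to the 4.3 list the efficacy items that the flowchart marks at visit 6: lesion size with epithelialization and infiltration, photograph and parasitology.

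The criteria for stopping and for rescue treatment do not change. The cost is protocol wording and, for early stoppers, a few more visits that are already in the schedule. No new procedure is needed.
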